### Dutch Meaningful Roles program

The Dutch adaptation of Meaningful Roles is a classroom-based program implemented by teachers. Teachers receive two three-hour training sessions from trained and experienced educational professionals. Meaningful Roles is an approach (throughout the schoolyear) for primary school groups 5 to 8 (children between 8–12 years old). The aim of Meaningful Roles is to improve the classroom climate and mutual relationships in the group, in a positive, prosocial way.

The program consists of three main components: meaningful roles, classroom meetings, and compliments (see Fig. 1 for the conceptual model). With regard to the roles, children are given specific roles to actively work on autonomy and responsibility, competence, and prosocial behavior. These roles, such as newsreader or plant caretaker, are prosocial in nature, because children help one or more children or are considerate of other children in the class. Moreover, roles give children autonomy and responsibility, as the children are free to perform the role as they see fit. The roles are aimed to optimize the strengths and talents of each child, through giving children the experience that they can contribute something that increases their confidence in their own abilities. During the weekly classroom meetings, children take the leading role in discussions about the classroom functioning and agreements: they discuss how they feel and what the atmosphere is like in the classroom. This ensures interaction and connection with each other and stimulates children’s feeling of competence, autonomy and responsibility in social classroom processes. Last, children learn how to give and receive effective compliments and practice with doing so on a structural basis, which strengthens trust in others and reinforces confidence in one’s own abilities.

### Control condition

The control condition will not receive any material or training concerning Meaningful Roles during the implementation of the program in the intervention condition (treatment-as-usual, TAU). Schools in the control condition are given the option to receive the materials and training to implement the intervention at a later stage, after the data collection is finished.

### Instruments

#### Primary outcomes

*Prosocial behavior* will be measured by several instruments measuring different domains (i.e., injunctive norm, individual prosocial behavior, sociometric nominations, cooperation in the classroom and conflict in the classroom).

Prosocial behavior as an injunctive norm (i.e., children’s attitudes towards prosocial behavior that are on average held in the classroom; [35]) will be assessed with three items specifically developed for this study (i.e., What can make you popular in your class?: “Helping each other”, “Being nice to each other” or “Working together”), rated on a 3-point scale from 1 (*not true*) to 3 (*definitely true*). Higher scores reflect a higher injunctive norm of the group towards prosocial behavior.

Individual prosocial behavior will be measured with the subscale prosocial behavior of the Strengths and Difficulties Questionnaire (SDQ), Dutch version [36], adapted for the current study. Four items are used (e.g., “I try to be nice to my classmates”), rated on a 4-point scale from 1 (*never*) to 4 (*always*). The SDQ-Dutch has sufficient psychometric properties in a children sample, with a Cronbach’s alpha of 0.78 for the total scale and 0.62 for the prosocial subscales [37]. Higher scores reflect more prosocial behavior.

Prosocial behavior according to children’s classmates will be measured with sociometric nominations. For each question, children see a list with the names of all classmates and select the classmates that fit the question best according to them [38]. Two items are used (i.e., “Which classmates help you with assignments (for example with math or language)?” or “Which classmates help you with problems (for example, when you are sad)?”). For each child, the number of received nominations was divided by the number of possible nominations (i.e., number of classmates), resulting in a proportion score for prosocial relations [39].

Cooperation and conflict in the classroom will be measured with the Classroom Peer Context Questionnaire (CPCQ), subscales cooperation and conflict, respectively [38, 40], rated on a 4-point scale ranging from 1 (*not true*) to 4 (*completely true*). The cooperation subscale consists of four items assessing the extent to which children experience positive behavior (e.g., “In this classroom, children help each other”). The conflict subscale consists of four items assessing the extent to which children experience negative behavior. For the current study, two items are used (i.e., “In this classroom, children are unkind to each other” and “In this classroom, children bully each other”). The CPCQ has adequate psychometric properties in a children sample, with a Cronbach’s alpha of 0.79 and 0.83 for the cooperation and conflict subscale, respectively [38]. Higher scores on the cooperation subscale reflects more positive behavior, while for the conflict subscale it reflects more negative behavior.

*Intrinsic (prosocial) motivation* will be measured with four items specifically developed for this study (e.g., “I think it is important to help someone” or “I want to know how to be a good friend”), rated on a 3-point scale ranging from 1 (*not true*) to 3 (*definitely true*). Higher scores reflect more intrinsic (prosocial) motivation.

*Social competence* will be measured with items based on the Rosenberg Self-Esteem Scale (RSES), Dutch version [41, 42]. Five items are used (e.g., I think positively about myself), rated on a 3-point scale ranging from 1 (*not true*) to 3 (*definitely true*). The Dutch RSES showed high internal consistency in adults [41] and sufficient psychometric properties in adolescent samples [43, 44]. Higher scores reflect more perceived social competence.

*Social autonomy* will be measured with items based on the School as a Caring Community Profile-II (SCCP-II; (Lickona and Davidson. School as a caring community Profile II, unpublished)) and the Child Development Project [34, 45]. Five items are used (e.g., “In this classroom, children help with making group appointments” or “In this classroom, you can choose how you want to do something”), rated on a 4-point scale ranging from 1 (*never*) to 4 (*always*). Higher scores reflect more social autonomy.

*ocial relatedness* will be measured with items of the Classroom Peer Context Questionnaire (CPCQ), subscales comfort and cohesion [38, 40], rated on a 4-point scale ranging from 1 (*not true*) to 4 (*completely true*). The comfort subscale consists of four items assessing the extent to which children feel at ease in the classroom (e.g., “In this classroom, I can be myself”). The cohesion subscale consists of four items assessing the extent to which the children in the classroom spend time together. For the current study, two items are used (i.e., “In this classroom, everyone likes each other” and “In this classroom, everyone belongs to the group”). The CPCQ has adequate psychometric properties in a children sample, with a Cronbach’s alpha of 0.83 and 0.68 for the comfort and cohesion subscale, respectively [38]. Higher scores on both subscales reflect more positive behavior.

#### Secondary outcomes

*School wellbeing* will be measured with eight items specifically developed for this study, assessing school belonging (7 items; e.g., “I like going to school” or “It is fun and nice in the classroom”), rated on a 4-point scale ranging from 1 (*never*) to 4 (*always*) and school safety (i.e., “I feel safe in and around school”), rated on a 5-point scale ranging from 1 (*very unsafe*) to 7 (*very safe*). Higher scores reflect positive school wellbeing.

*Social position* will be measured with sociometric nominations. For each question, children see a list with the names of all classmates and select the classmates that fit the question best according to them [38]. Questions are related to kindness (i.e., “Which classmates do you like?”, leadership (i.e., “Are there any children in your class who are leaders?”), unkindness (i.e., “Which classmates do you not like at all?”), popularity (i.e., “Which children in your class are popular?”), and best friends (i.e., “Which classmates are your best friends?”). For each child, the number of received nominations was divided by the number of possible nominations (i.e., number of classmates), resulting in a proportion score for each social position (i.e., five proportion scores) [39].

*Bullying and victimization* will be measured by assessing bullying and victimization with a selection of items of the Olweus Bully-Victim Questionnaire, Dutch version (OBVQ; [46]) and sociometric nominations. The OBVQ consists of items related to bullying, bullying victimization, and the perceived behavior and attitudes of the teacher. Two questions are examined, related to bullying (“How often have you bullied other children in the past few months?”) and bullying victimization (“How often have you been bullied in the past few months?”). Responses are rated on a 5-point Likert scale: *I did not bully/I was not bullied*, *only once or twice*, *two or three times a month*, *about once a week*, and *several times a week*. Seven additional questions relate to bullying victimization, and ask about behaviors that are associating with bullying (e.g., “I was called names, ridiculed or laughed at” or “I was threatened or forced to do things I did not want to do”), rated on 5-point Likert scale ranging from 1 (*not at all*) to 5 (*several times a week*). One additional item asks where the child is bullied (e.g., “In the hall or corridor”, “During gym class” or “In another place”). Three items relate to the perceived behavior and attitudes of the teacher (i.e., “Has your teacher ever mentioned bullying during class?”, with answer options: no, once, 2–4 times, 5–8 times, more than 8 times’, “What does your teacher think about bullying?”, with answer options: it is a good thing, it does not matter, I do not know, it is a bad thing, it is a very bad thing, and “What can your teacher do to stop bullying?”, with answer options: nothing, very little, a little, a lot, very much). Answer options will be recalculated so that higher scores reflect more bullying, victimization, and negative attitudes/behavior of the teacher. The OBVQ showed adequate psychometric properties in children samples, with a Cronbach’s alpha above 0.80 [47–49]. Regarding sociometric nominations, ten questions related to bullying victimization and one question related to bullying will be asked to children (e.g., “Who starts bullying you”, “Who will participate if you are being bullied?” or “Which classmates help you when you are being bullied?”). For each question, children see a list with the names of all classmates and select the classmates that fit the question best according to them [38]. For each child, the number of received nominations was divided by the number of possible nominations (i.e., number of classmates), resulting in one proportion score for victimization (i.e., sum of all ten items) and one for bullying [39].

*Civic skills* will be assessed at all three timepoints, for teachers only. Specific questions were developed for this study, based on the questionnaire measuring citizenship ([Vragenlijst Burgerschap Meten]; [50]). Four domains will be assessed by asking teachers how the children in their class: 1) act democratically (e.g. “accept decisions made by the whole class (majority decisions)”, 2) act socially responsible (e.g., “stand up for each other”), 3) dealing with conflicts (e.g., “consider the other person in a conflict when looking for a solution”, and 4) dealing with differences (e.g., “are curious about what other children are good at (qualities)”. Higher scores reflect more (positive) civic skills in the classroom.

*Teacher attitudes* will be assessed at all three timepoints, with specific questionnaires developed for this study. Teachers are asked what they find important in their job as a teacher to stimulate, for example: “that children help each other in the classroom”. Higher scores reflect a positive attitude of stimulating prosocial behavior and STD components.

#### Moderators

*Child, teacher, and school characteristics* will be collected at baseline. Child characteristics include age, gender, romantic attraction (i.e., possibility of falling in love with a boy/girl), grade, and ethnic identity. Teacher characteristics include age, gender, years of experience (as a teacher in general, and as a teacher at the specific school) and experience with implementing social safety programs, as well as attitudes of the teachers. School characteristics include location, number of participating grades and students in the classrooms, and years of experience with a social safety program (e.g., KiVa).

*Working elements* will be assessed halfway through the program (T2) and after completion of the program (T3), with specific questions developed for this study. Children and teachers fill in questionnaires related to the three main components of the program: 1) meaningful roles (e.g., “How much did you like the role(s)”, “Which roles were the most popular?”, respectively), 2) classroom meetings (e.g., “The weekly meetings were done independently by the class”, “How often has a meeting been held?”, respectively), and 3) compliments (e.g., “I have received compliments from my classmates”, “How many times a week has attention been paid to the compliments?”, respectively). Higher scores reflect a more positive or greater adherence of the working elements.

*Program integrity* will be assessed halfway through the program and after completion of the program, with specific questions developed for this study. Teachers and school leaders fill in (open and closed) questionnaires related to the implementation of the program, divided into the domains training and material (e.g., “How often have you used the manual?”), child questionnaires (e.g., “Where there any questions that the children struggled with?”), time investment (e.g., “How did you feel about the time you had to implement the program properly?”), and global impression (e.g., “What is your general impression of the degree of success of the implementation of the program?”). Higher scores reflect a more positive or greater adherence of the program.

#### Teacher focus groups

In addition to the questionnaires, focus groups for teachers will be organized at T1, T2, and T3 to evaluate the implementation of Meaningful Roles. One delegate teacher per school will be asked to participate in these focus groups. Delegates can talk about their experiences with the intervention program and research, and are encouraged to make suggestions about important questions that should be included in the data collection waves for teachers and school leaders (at T2 or T3), in order to understand how feasible the implementation has been and what should be improved about the program. Semi-structured interviews will be used for the focus groups. The purpose of these focus groups is thus threefold: 1) information can be used as an indicator of the process evaluation (qualitative research information as an addition to the questionnaires) to understand strengths and difficulties in the execution of the intervention and evaluation of the research. This information can also help to understand why stronger or weaker effects may be found in different schools (i.e., interpretation of effects); 2) information can be used to give suggestions for improving the program in the future; and 3) information can be used to add any questions to the intermediate measurement (T2) and final measurement (T3) that, in the experience of the teachers, seem important to measure regarding the implementation (not the outcomes). These findings are used to clarify the findings in the context of the implementation process.

### Statistical analyses

Before the analyses, possible baseline (T1) differences in demographics and outcome variables (baseline assessment) between children in the intervention program and the control condition will be checked with ANOVA (continuous variables) and chi-square analyses (categorical variables). To investigate the effectiveness of the intervention program, regression analyses will be performed. The dependent variables are the outcome measures at intermediate (T2) or posttest (T3), condition is the predictor variable (1 = intervention, 0 = control), and baseline (T1), potential differences between the experimental and control group at T1, or intermediate measures (when dependent variables are the outcome measures at T2) are the covariates. The effect of potential moderators (categorial or continuous) on the outcomes will be examined by adding interaction effects to the models.

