## Methods

### Design

A cluster RCT will be conducted. Schools will be randomized (stratified for number of participating classrooms) into the intervention condition in which the program starts immediately or into a control condition that receives the program one school year later (see Fig. 2), using an online randomization tool [33] in a 1:1 ratio. We will recruit a diverse sample of children from primary schools in the Netherlands.

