### Study sample

We aim to include *N* = 42 schools to ensure there is enough power for the analyses (*N* = 21 schools for both the intervention and waitlist control condition). This sample size is sufficient to examine the effectiveness of Meaningful Roles and potential moderators, with a power of 0.80, an alpha of 0.05 and a medium effect size of 0.21 [18].

Participants are children from the upper grades of primary school (grades 5–8) in the Netherlands, their teachers (who will implement the program) and school leaders. The children will mostly be between 8 and 12 years old.

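### Schools are randomised, but the stated regression model has no school or class term, so as written the tests of condition reject too often

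*Protocol article*

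**What the plan says.** Design states that "A cluster RCT will be conducted" and that "Schools will be randomized (stratified for number of participating classrooms) into the intervention condition" or a delayed-start control. Study sample sets the target as "42 schools to ensure there is enough power for the analyses", with "21 schools for both the intervention and waitlist control condition". The school is therefore the unit of allocation.

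Statistical analyses then gives the methods. Baseline differences in demographics and outcomes "between children in the intervention program and the control condition will be checked with ANOVA (continuous variables) and chi-square analyses (categorical variables"). For the effect itself, "To investigate the effectiveness of the intervention program, regression analyses will be performed". The section goes on to list what enters the model:

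- the outcome at T2 or T3 as dependent variable;
- condition, coded 1 or 0, as predictor;
- the T1 value, any T1 differences between the arms, or intermediate measures as covariates;
- interactions for the moderators.

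Neither this section nor any other mentions school or class as a model level, a random effect, generalised estimating equations, cluster-robust errors or an analysis of cluster summaries.

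**The concern.** Children sit in classes and classes sit in schools. Several primary outcomes make correlation within a class close to inevitable: the cooperation, conflict, comfort, cohesion and autonomy items ask the child to describe the shared classroom, and the injunctive norm is defined as an attitude held on average in the class (Instruments, Primary outcomes). The programme is also delivered to the whole class by its teacher.

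If the listed model is fitted to children as independent units, the standard error for condition reflects the number of children instead of the 42 schools. Chance differences between schools can then be reported as a programme effect.

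The problem spreads in two ways. The baseline tests carry the same inflation, and they help decide which covariates enter. Moderator interactions are added to the same models, so moderators measured on teachers or schools inherit the error.

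**Working it through.** **The plan's own figure.** Inputs from Study sample: effect size 0.21, alpha 0.05 (two-sided assumed), power 0.80, 21 schools per arm. Without clustering, n per arm = 2 × (1.96 + 0.84)² / 0.21² ≈ 356 children, or 356 / 21 ≈ 17 per school. With m children per school, 21 schools per arm fits ICC = (21m/356 − 1)/(m − 1), which is 0.0095 at m = 20 and 0.043 at m = 60. The 42 schools can be neither confirmed nor refuted, because m and the ICC are not stated.

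**Size of a child-level test, no baseline adjustment.** Assumed: m = 20 or 60, ICC 0.01 to 0.10.

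- Design effect: DE = 1 + (m − 1) × ICC.
- Actual type I error of a nominal 5% test: 2 × [1 − Φ(1.96/√DE)].

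| m | ICC | DE | √DE | Formula | Simulation |
|---|---|---|---|---|---|
| 20 | 0.01 | 1.19 | 1.09 | 7.2% | 7.3% |
| 20 | 0.05 | 1.95 | 1.40 | 16.0% | 15.3% |
| 20 | 0.10 | 2.90 | 1.70 | 25.0% | 25.1% |
| 60 | 0.01 | 1.59 | 1.26 | 12.0% | 11.8% |
| 60 | 0.05 | 3.95 | 1.99 | 32.4% | 33.2% |
| 60 | 0.10 | 6.90 | 2.63 | 45.6% | 44.9% |

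The simulation used 21 schools per arm and 4,000 null trials per setting. A t-test on school means held 4.5–5.4% throughout.

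**Adding the class level.** Let s and c be the school and class ICCs, with 20 children per class. For one class per school, DE = 1 + 19(s + c). For four classes per school, DE = 1 + 19(s + c) + 60s.

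| s / c | DE, one class | Type I | DE, four classes | Type I |
|---|---|---|---|---|
| 0.01 / 0.04 | 1.95 | 16% | 2.55 | 22% |
| 0.02 / 0.05 | 2.33 | 20% | 3.53 | 30% |
| 0.05 / 0.05 | 2.90 | 25% | 5.90 | 42% |
| 0.05 / 0.10 | 3.85 | 32% | 6.85 | 45% |

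**Adjusting for T1.** If the T1–T3 correlation is the same at every level, adjustment leaves the residual ICC unchanged and the table above applies approximately. If school and class effects are more stable over time than children's own scores, the residual ICC falls. Simulated T1-adjusted regression over the same four ICC pairs (42 schools, child-level correlation 0.5) gave:

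- four classes of 20: 25–43% with a cluster-level correlation of 0.5, and 17–38% with 0.8;
- one class of 20: 15–33% and 10–23% respectively;
- school-mean analysis: 4–6%.

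These agree with the formula to within a few percentage points of simulation error.

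**Power once clustering is respected.** With 21 schools per arm, m = 60, effect 0.21, a normal approximation and no baseline adjustment, power is about 0.99 at ICC 0.01, 0.76 at 0.05 and 0.52 at 0.10.

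**The case against.** The strongest reply is that the article never says ordinary, single-level or child-level regression. Multilevel regression is also regression, the section is a short summary, and a fuller analysis plan may exist. The authors call the study a cluster trial, stratify by number of classrooms and set the sample size in schools, and 21 schools per arm is compatible with a cluster-adjusted calculation.

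This stands in part. A reader might infer that the trial has committed itself to ordinary least squares on children, but the documents do not establish that. The child is the explicit unit only for the baseline checks; for the effect models it is inferred from the listed terms. Nor does the absence of an ICC in Study sample show that the analysis ignores clustering, since an article commonly leaves that figure to the full protocol.

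A reader might also infer that the error is always severe and that every p-value is worthless. That too is unsupported. School size is not given, participation of all upper classes is only a preference, and parental consent is active. At 20 children per school and ICC 0.01 the inflation is modest.

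What does not stand is the defence that this is detail left for later. The section names the tests and lists the model terms, and that list does not match the unit of randomisation.

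**Conclusion.** The point holds in this form: the stated model has no school or class term although schools are randomised, and followed as written it gives standard errors for condition that are too small. The direction is certain for any positive residual ICC.

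The size is assumed, not documented. It runs from about 7% in the mildest case (unadjusted, 20 children per school, ICC 0.01), through about 10–33% with one class of 20 per school, to about 17–43% with four classes of 20. The last two ranges are T1-adjusted, for school/class ICCs from 0.01/0.04 to 0.05/0.10, a child-level T1–T3 correlation of 0.5 and a cluster-level correlation of 0.5 to 0.8. An analysis that respects school gives about 5%. Because all child-reported primary outcomes use this model, the text should be corrected before outcome data are analysed.

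**What to change.** In Statistical analyses, replace the unspecified regression with multilevel regression:

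- children within classes within schools, with random intercepts for class and school;
- the T1 value of the outcome as covariate;
- small-sample degrees of freedom, such as Satterthwaite or Kenward-Roger;
- classes within schools for teacher-reported outcomes.

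A T1-adjusted analysis of school means can serve as a check on the main effect of condition. It cannot replace the multilevel model, because it cannot properly test the child-level moderators (age, gender, grade, ethnic identity).

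Report baseline comparisons descriptively. At the least, do not choose covariates from child-level baseline tests that ignore clustering.

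The cost is wording and no new data, but the change has consequences. Confidence intervals become wider, and correctly so. The 0.80 power in Study sample should be checked against the clustered model, with the ICC and cluster size stated.
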